## Abstract

**Background:**

The effective treatment of patients with severe psychiatric disorders primarily relies on subjective reporting of symptoms and side-effects. This information is crucial for a clinician's decision regarding medication adjustment. Treatment adjustment usually happens at a low frequency (∼4–8 weeks). In between points of care, patients are left alone with their symptoms and side-effects. This leads to uncertainty regarding the treatment, non-adherence, possible relapse, and rehospitalization.

**Objectives:**

We aim to design a flexible electronic patient-reported outcome (ePRO) system, which allows patients with severe psychiatric disorders to: (a) record their symptoms using an app; (b) share the data with the clinical team at points of care; and (c) utilize the data to support therapy decisions.

**Methods:**

In this article, we describe the development process which included the following steps: (a) formation of a co-design team; (b) stakeholder interviews with patients, practitioners, and digital health experts to access needs, requirements, and barriers; (c) prototype conceptualization and design; (d) user acceptance testing and refinement; and (e) finalization of the system for testing in a pilottrial.

**Results:**

We included input from patients with lived experience of psychiatric disorders, clinical team members, software engineers, and researchers. A prototype system was refined, and iterative changes were made before finalization during a series of operational meetings. The system allows patients to digitally self-report their symptoms and provides longitudinal ePRO symptom data for export into the electronic health record.

**Conclusions:**

Routine ePRO collection has the potential to improve outcomes and hereby also reduce health service costs. We have successfully developed a trial-ready ePRO system for severe psychiatric disorders. The findings were incorporated in the planning of a feasibility pilot trial. Assuming feasibility will be established, the system might be subjected to a certification process evaluation of safety and efficacy including a randomized controlled trial.

## Introduction

Mental illnesses have a high prevalence,^
1
^ leading to significant impairments on an individual and societal level,^
2
^ and high treatment costs.^
3
^ Particularly, severe mental illnesses (SMI), such as bipolar disorder, schizophrenia, major depressive disorder, and anorexia nervosa are characterized by recurring episodes, chronic trajectories, and frequent rehospitalization.^
4
^

Since treatment response and relapse prediction in mental health are complex, outpatient treatment remains challenging. Outpatient psychiatrists face the task of caring for many patients in routine clinical practice. Consequently, appointments are kept short^
5
^ and low in frequency leaving patients^5–7^ and clinicians^
7
^ unsatisfied. From a patient's point of view, summarizing their condition, life events, medication intake and effects, and possible side-effects during a short appointment is challenging. On the other hand, practitioners have to quickly identify interactions and possible correlations between the various factors and draw treatment conclusions (general practitioners use more time for patients with mental health problems than for patients with somatic problems^
8
^). An app-based companion that allows patients to record their symptoms and medication side-effects in between points of care and that additionally helps to present the data at the next appointment might alleviate these problems by allowing the practitioner to quickly assess symptom trajectories and therefore save time for discussion of the further treatment course.^
9
^

Formalized reported outcome measures for evaluation treatment response, also referred to as measurement-based care,^
10
^ are recommended in guidelines and are proven to ameliorate service user activation,^
11
^ shared decision making,^11,12^ and treatment outcome.^13,14^ Even though the use of patient-reported outcomes (PROs) is increasing, in medicine as well as in psychotherapy^
15
^ and PROs are applicable in severe mental illness,^
16
^ PROs are rarely implemented in routine care^
17
^ due to limited time.^
18
^

In ambulatory psychiatric care, treatment non-responders as well as side-effects of medication are often not recognized fast enough, which leads to poor patient–physician relationship,^
19
^ non-adherence to therapy, and ultimately, rehospitalization.^
20
^ Measurement-based care might help to detect non-responders and relapses earlier and therefore improve outcomes.

While asking patients to regularly complete validated, self-report questionnaires provides a more comparable estimate of symptom change, validated self-reports might not inform about subtle changes in an individual's psychopathology and functioning as well as being burdensome for patients and clinicians.^
21
^ Moreover, since treatment goals, especially in a recovery-oriented setting, are highly individual, an equally personalized method of tracking goal attainment progress is warranted.^
22
^ Finally, adherence to digital applications may be higher than to paper-pencil solutions.^
23
^

Questionnaires filled out during patients’ visits may not provide the necessary temporal resolution for detecting symptom changes or side-effects and are subject to recall bias.^24,25^ Repeated electronic recording of momentary states between points of care (ecological momentary assessment) might provide necessary data for readily detecting and visualizing symptom changes and side-effects of pharmacotherapy—both for patients and for clinicians with high temporal resolution.^
26
^ This seems to be a suitable way to enable a more accurate recording of psychiatric symptoms with a higher ecological validity and may allow equally precise diagnosis as established rating scales^
27
^ or might even allow new diagnostic classifications (digital phenotyping^
28
^).

In this study, we seek to analyze the potential and preconditions for a digital solution that uses the collection of customizable electronic patient-reported outcome (ePROs) to support treatment in psychiatric outpatient clinics (RecoveryCat). We hypothesize that a smartphone-based digital mental health application (DMHI) for recording ePROs has the potential to capture and transfer accurate information on symptom trajectories despite low-frequency and short treatment appointments and that the collected information can be helpful in the process of shared decision making. Specifically, ePROs may allow the detection of subclinical trends in symptoms that act as early relapse predictors. Short-term effects between medication dose adaptation and symptom or medication side-effect changes may become comprehensible. Perspectively, regular symptom tracking may allow differentiation of specific treatment effects and symptom fluctuation due to other causes.^
29
^

The DHMI for patients and practitioners will help to routinely use ePROs in clinical practice and establish the implementation of the use of an app in clinical practice, putatively increasing sustained use by patients,^
30
^ eventually for further extensions (e.g. an alert system and a crisis plan connected to the symptoms of the patient).

In this exploratory study, we assess the feasibility and determine key user experience design and app architecture in a multi-stakeholder approach (patients, mental health practitioners, and health insurance providers). Principles of user-centered design were applied both on practitioners’ as well as patients’ side^31,32^ as users were involved in all phases of development (stakeholder interviews, prototype development, and prototype testing). Results of our mixed methods approach and the technical translation of the findings will be presented in a narrative summary. We will discuss possible add-ons and a scope of possible applications.

## Methods

For the development of a flexible, electronically assessed patient-reported outcome tool as described above, we chose the following three phase user-centered design (UCD) research and development strategy.^
33
^ UCD implies involvement of users at all stages of the development process to ensure needs, preferences, and limitations of the end users are met.^
34
^

### Phase II: prototype development

The prototype development team defined typical users in the form of personas to give transparency to all team members for whom and which needs the application to be developed for.^
37
^ The main user insights were then turned into requirements for the app on two levels: the actual features as well as user experience design aspects, such as level of individualization of the questions or user flows. The prototype development team (design in teams^
32
^) turned the requirements into simple wireframes (application screens without building the actual application technically, first) in order to be reevaluated by interviewed stakeholders.

### Phase III: prototype testing

User acceptance testing of the developed workflow and features was conducted with 11 patients and 11 practitioners at two outpatient clinics using the prototype wireframes. We chose an open testing approach in which we presented wireframes to the users and asked them to think aloud^38,39^ while going through the screens. We observed how users would navigate through the app and understand its functions and usefulness. Iterative changes were made to the ePRO system draft in response to the findings. An iterative user-centered design methodology was repeatedly applied for further refinement of the concept in this early development phase.^
40
^

## Results

### Stakeholder interviews

In the following section, we will present the central and repeatedly mentioned topics of the stakeholder interviews.

Patients (n = 11) reported feeling stressed and partly overwhelmed before and during a point-of-care situation with their physician (4/11). A lot of information about symptom development, side-effects, and drug intake within a period of weeks needs to be remembered and shared within minutes, in order to provide meaningful data for the practitioner to make a suggestion for future treatment. Our stakeholder interviews revealed that there is a high need for monitoring symptoms and side-effects by patients in order to better understand their own recovery (6/11), have more informed conversations with their practitioners, and detect signs of relapse or crisis early (6/11). Some patients (3/11) already use paper-pencil methods or Excel-sheets for this purpose, but these were described as inconvenient to use during daily routine, and difficult to share with practitioners. Another important finding around symptom monitoring was that questions need to be highly personalized (4/11) and should not only refer to symptoms, but also recovery resources (7/11). Patients reported to have discontinued monitoring because they could not relate to the questions asked or even specific terms used in standardized questionnaires (2/11). A few patients expressed concerns about data privacy (2/11).

Practitioners (n = 11) emphasized the necessity of monitoring applications that are integrated into everyday clinical routine (11/11). Such apps should be easy to use (5/11) and deliver specific and meaningful data (4/11). Some practitioners reported having used digital tools or workarounds with their patients (6/11) for years or even decades to gather data in between points of care, for example asking patients to send daily emails rating their symptom severity (1/11). Our interviewees also stressed the mismatch of traditional paper-pencil rating scales for monitoring symptoms over time (4/11). Concerning the adaptability of the PROs, multiple practitioners mentioned a preference for higher adaptability as opposed to standardization (4/11). Practitioners generally favored DMHIs with integrability into routine outpatient care (5/11). Two practitioners expressed concerns about therapeutic standalone applications, solely used by patients independently of their treatment, because of the intransparency of the parallel therapeutic processes patients engage with (2/11).Our interviews also revealed a clear implementation barrier for our app to be used on a frequent basis by practitioners: A digital tool should not produce extra work in points of care but ideally assist the doctor and therefore be time saving by facilitating information exchange (3/11).

Digital health experts (n = 4) were additionally interviewed to make sure to achieve product-market fit beyond meeting user needs in the future. They were recruited for interviews through the network of the Digital Health Accelerator program of the Berlin Institute of Health, which presupposes relevant past experience in the field of digital health. We surveyed mental health tech founders focusing on SMI. Up to today, we found only two monitoring or journaling tools for patients with SMI: eMoods,^
41
^ an application for individuals with bipolar disorder and recovery record^
42
^ for patients with eating disorders. eMoods has around 50,000 active users without marketing activities, proving the need for this target group to follow up their symptoms on a daily basis. Recovery record has about 600,000 users.^
42
^ Further, regulatory experts stressed the importance of validated ePRO for proving efficacy, next to data safety, and quality control aspects.

### System architecture

Because of the sensitivity of the data and the particular and legitimate skepticism of patients and therapists towards digital solutions, data protection is crucial. As key components to address the issue, we chose encryption and decentralized data storage, i.e. insufficiency as a feature: Data only resides on the end user's device and data transmission only happens encrypted and when actively triggered by the user. The app handles two kinds of sensitive data: questions along with answer options and answer schedules on the one hand and the patient's answers on the other hand.

For data transmission, the sender selects the data and the app will generate a QR code that includes a secret key and channel name on our web socket server to allow communication between the web browser and the server. The recipient scans the QR code and both app instances (i.e. the patient and clinician versions) meet on the websocket server. The two parties exchange connection data in order to establish a webRTC connection (Web Real-Time Communication, an open standard for communication from device to device) between the two devices and exit the server. The exchange of the connection data is encrypted with the key found in the QR code. The server cannot read any of the information. The actual user data is then transmitted encrypted through the webRTC connection, again using the secret key found in the QR code. If the webRTC connection cannot be established due to network connectivity issues, the transmission will fall back to transmit the user data through the server in the same way the connection data was transmitted before (as an exception which cannot be induced by the server). In any case, data will be end-to-end-encrypted with the key received through the QR code. The QR code will only be valid for a few minutes. Further use of the data in the electronic health record or hospital information system is planned; respective data privacy regulations apply.

We will develop the core of the software under a permissive open source license (Massachusetts Institute of Technology License). The app will be developed as progressive web app (browser based), in order to reduce access barriers. The ionic framework using angular will be deployed.

### Planning of a case–control pilot trial

After completing the design of the application as described, we plan to test it in a further study. As practitioners described a lack of applications for patients affected by severe mental illness, we are planning a study to investigate the applicability of app-based recording of PROs in patients suffering from bipolar disorder, schizophrenia, schizoaffective disorder, and severe recurrent major depression from clinical practice in two psychiatric institutional outpatient clinics.

The pilot study aims first of all to estimate the individual use (adherence, retention rate) and usability (system usability score,^
43
^ to estimate to what extent certain patient populations can be accompanied with the described procedure. We plan a case–control study design (see Figure 1) for pragmatic reasons, as we expect the design to be the most economic approach to address questions of feasibility and usability. The collected data will also inform the selection of the most suitable primary outcome measures for a future full-scale randomized controlled trial (RCT) and provide data and effect estimates for power calculation to help estimate the sample size for the full-scale RCT with a more refined prototype. We plan to include 60 patients in the intervention group and 60 patients in the control group. Due to the fact that the study is planned as a feasibility study, a power analysis is not applicable. Details on the study including inclusion and exclusion criteria, sample size as well as statistical analysis can be found in the preregistration (DOI 10.17605/OSF.IO/HGKJT; https://osf.io/hgkjt).

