**Figure 1 fig1-20552076231191009:**
[figure not shown]
Flow diagram of the planned multicenter case–control study. ARM: Altman Self-Rating Mania Scale; BDI: Beck Depression Inventory; CRF: case report form; ePROM: electronic patient-reported outcome measure; ES: Eppendorfer Schizophrenie Inventar (Eppendorf Schizophrenia Inventory); GAF: Global Assessment of Functioning scale; HAMD: Hamilton Depression Scale; PANSS: Positive and Negative Syndrome Scale; PHQ-9: Patient Health Questionnaire-9; WHO-QoL-Bref: World Health Organization Quality of Life Questionnaire; YMRS: Young Mania Rating Scale.

Concerning clinical endpoints, we chose indicators of quality of life World Health Organization Quality of Life Questionnaire (WHO-QoL-Bref^
44
^) and Recovery Quality of Life (ReQoL^
45
^), the Clinical Global Impression (CGI^
46
^) for overall symptoms and the Global Assessment of Functioning (GAF) as an indicator of functioning^
47
^ and the Empowerment-Promoting Assessment Scale (EPAS) for empowerment^
48
^ in all patient groups. Intelligence was estimated by the Wortschatztest (WST^
49
^). Diagnosis specific symptoms will be assessed with the Patient Health Questionnaire-9 (PHQ-9),^
50
^ Beck Depression Inventory (BDI),^
51
^ Hamilton Depression Scale (HAMD)^
52
^ for depression, Positive and Negative Syndrome Scale (PANSS)^
53
^ and Eppendorfer Schizophrenie Inventar (ESI)^
54
^ for psychosis, and Young Mania Rating Scale (YMRS)^
55
^ and Altman Self-Rating Mania Scale (ASRM^
56
^) for manic episodes. Self-rating scales and clinical rating scales were chosen to explore correlations of our ePRO items with self-assessment and clinical assessment. The approval by the Charité's ethics board was obtained for the conduct of the study.

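### The pilot is called case–control although its groups are an intervention group and a control group, and its between-group effect estimate should not feed the RCT power calculation

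*Protocol article*

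**What the plan says.** In the protocol article, the section on planning the pilot says "We plan a case–control study design (see Figure 1) for pragmatic reasons". The reason given is economy: "as we expect the design to be the most economic approach to address questions of feasibility and usability". The Figure 1 legend repeats the label ("Flow diagram of the planned multicenter case–control study"), and so do the section's own heading, the Limitations section and the section on potential benefits for pharmacotherapy.

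The same planning section describes the groups differently: "We plan to include 60 patients in the intervention group and 60 patients in the control group". The text under Figure 1 then lists clinical endpoints to be assessed: quality of life, global impression, functioning, empowerment and diagnosis-specific symptom scales.

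On purpose, the section puts use and usability first: "The pilot study aims first of all to estimate the individual use (adherence, retention rate) and usability". It adds that the data will inform the choice of primary outcome for a later RCT and will "provide data and effect estimates for power calculation to help estimate the sample size for the full-scale RCT". On sample size it says "Due to the fact that the study is planned as a feasibility study, a power analysis is not applicable". Further details, including the statistical analysis, are left to the preregistration.

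**The concern.** Two things do not fit together.

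First, a case–control study samples people by outcome or disease status and compares earlier exposure. Here the groups are named by intervention, and clinical outcomes are then measured. The label therefore contradicts the description, and it recurs too often to be a slip.

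Second, the article hands the pilot's effect estimates to the RCT power calculation. If patients enter the two groups by something other than chance, the difference between groups mixes any effect of the app with differences between the patients. The article itself names plausible selection factors: scepticism towards digital solutions (System architecture), privacy concerns (Stakeholder interviews) and affinity for technology (Limitations). An RCT sized on a distorted or very noisy difference could be badly under- or over-sized.

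**Working it through.** **Step 1. Design name against design description.**

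| Feature | Case–control study | This pilot, as described |
|---|---|---|
| Groups defined by | outcome or disease status | intervention or control, 60 each |
| What is then measured | past exposure | clinical endpoints |

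The description matches a controlled intervention study. No calculation is needed for this part.

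**Step 2. Allocation.** The article mentions randomisation only for the future RCT and gives pragmatic and economic reasons for the pilot design. Non-random allocation is the natural reading. No sentence states it, and none describes matching or adjustment.

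**Step 3. The plan's own figure.** The 60 + 60 = 120 cannot be reproduced, because the article gives no alpha, power, effect size or SD and declares a power analysis not applicable. No stated figure is therefore wrong. What follows is illustration.

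**Step 4. Effect of a bias on the RCT size.** Assumptions, none taken from the article: SD = 1, two-sided alpha 0.05, power 80%, 1:1 allocation, normal approximation.

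- Size: n per arm = 2(1.960 + 0.842)² / d² ≈ 15.70 / d², rounded up.
- True power when the true effect is δ: Φ(δ / √(2/n) − 1.960).

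Take a true effect of 0.30:

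- No bias: 15.70 / 0.30² gives 175 per arm.
- Bias +0.1, pilot shows 0.40: 15.70 / 0.40² gives 99 per arm. True power = Φ(0.30 / √(2/99) − 1.960) = Φ(0.15) ≈ 56%.
- Bias −0.1, pilot shows 0.20: 15.70 / 0.20² gives 393 per arm. True power = Φ(0.30 / √(2/393) − 1.960) = Φ(2.25) ≈ 99%.

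The same calculation over a range of true effects:

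| True effect (SD) | Needed per arm | Planned with bias +0.1 (true power) | Planned with bias −0.1 (true power) |
|---|---|---|---|
| 0.2 | 393 | 175 (46%) | 1,570 (above 99%) |
| 0.3 | 175 | 99 (56%) | 393 (99%) |
| 0.4 | 99 | 63 (61%) | 175 (96%) |

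**Step 5. Precision without any bias.** For a standardised difference of 0.30 with 60 per group, the 95% half-width is 1.960 × √(2/60 + 0.30²/(2 × 120)) = 1.960 × √0.03371 ≈ 0.36. An observed 0.30 would carry an interval from 0.30 − 0.36 = −0.06 to 0.30 + 0.36 = 0.66, which includes zero. Dropout would widen it.

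**Step 6. Which aims are touched.** App adherence, app retention and the usability score are estimated within users of the app. They do not depend on the contrast between groups.

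**The case against.** The strongest reply is that this is a feasibility pilot described in a condensed article. Its leading aims do not rest on the comparison. The effect estimates are only to help with sizing an RCT of a more refined prototype, and are not said to be the sole input. Allocation, matching and adjustment are details that an article may leave to the preregistration. Figure 1, which might show the flow, is also not shown.

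Much of this stands, and it rules out several stronger readings that a reader might infer:

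- *That allocation is certainly non-random.* Groups in a randomised trial are also defined by the intervention, so the wrong label does not prove it.
- *That the estimates will be confounded, and the RCT therefore too small.* Only a risk can be shown. Its direction is unknown, and adjustment may be planned.
- *That the controls contribute nothing to the stated aims.* The article does not say what controls receive. Their data could still inform outcome selection, variability and completeness of assessment.
- *That the label will lead to an analysis of exposure odds.* Nothing in the text points that way, since the section heading also says pilot trial.
- *That the pilot must be randomised.* A non-randomised feasibility pilot is a legitimate choice. Patient and clinician run the workflow together, so randomising within clinics could bring contamination if the same clinicians treat both groups. Randomising would also leave the ±0.36 SD imprecision untouched.

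The reply does not rescue the design name, which is an error in the article itself. Nor does it justify using the effect estimate as a power input, because the imprecision remains whatever the preregistration says about adjustment.

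**Conclusion.** The point holds in a limited form. The design name is wrong as written. Allocation appears non-random, but this is inferred. The between-group estimate is open to selection bias in either direction and is too imprecise at 60 per group to set the effect size of the RCT.

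The size is illustrative. With an assumed true effect of 0.30 SD, a bias of only 0.1 SD moves the planned RCT from 175 per arm to 99 (true power about 56%) or to 393. The half-width of about ±0.36 SD is more than three times that bias. These figures rest on SD = 1, two-sided 5%, 80% power and 1:1 allocation, none of which the article supplies. The adherence, retention and usability aims are not affected.

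**What to change.** 1. Replace case–control with the correct design name wherever it appears: the planning section and its heading, the Figure 1 legend, Limitations, and potential benefits for pharmacotherapy. If allocation is indeed non-random, *prospective non-randomised controlled pilot* would serve.
2. State in one sentence how patients enter each group, consistent with the preregistration.
3. In the planning section, remove effect estimates from the inputs to the RCT power calculation. Carry forward SDs, baseline–follow-up correlations, retention and completeness of assessment, and base the RCT effect size on a clinically relevant difference. The pilot difference can still be reported descriptively with its confidence interval.

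The cost is wording, plus giving up a pilot-based effect size for the RCT.

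The investigators may also consider randomising the pilot, for example 1:1 within clinic, which would test willingness to be randomised. That would need an amendment, some patients who want the app would not receive it during the pilot, and contamination would have to be weighed. It is an option, not a required correction.

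### The pilot's between-group effect estimate should not size the later RCT: at 60 per group it is too imprecise, it may be biased for the RCT's effect, and the same data also inform the choice of outcome

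*Protocol article*

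**What the plan says.** All the planning statements are in the protocol article, Results, section on planning the case–control pilot trial.

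- Size: "We plan to include 60 patients in the intervention group and 60 patients in the control group". On its basis: "Due to the fact that the study is planned as a feasibility study, a power analysis is not applicable".
- Design: "We plan a case–control study design (see Figure 1) for pragmatic reasons". The article gives economy in answering feasibility and usability questions as the reason. It does not describe the allocation as randomised, and it sets the pilot apart from a later RCT.
- First use of the data for the RCT: to "inform the selection of the most suitable primary outcome measures for a future full-scale randomized controlled trial (RCT").
- Second use: to "provide data and effect estimates for power calculation to help estimate the sample size for the full-scale RCT with a more refined prototype".

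The text under Figure 1 lists five clinical endpoints for all patients (WHO-QoL-Bref, ReQoL, CGI, GAF, EPAS). It adds seven diagnosis-specific scales: PHQ-9, BDI and HAMD for depression, PANSS and ESI for psychosis, YMRS and ASRM for mania. The article gives no rule for choosing among them. It refers details of sample size and analysis to a preregistration that is not shown.

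**The concern.** Sizing an RCT on a pilot's observed effect carries the pilot's sampling error straight into the RCT's sample size. An overestimate gives an RCT that is too small, an underestimate gives one larger than needed, and an estimate at or below zero gives no usable size. The article treats 60 + 60 as a feasibility number, yet assigns these data an effect-estimation task.

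Two features add to the imprecision. The pilot contrast may be confounded, and the RCT will test a changed product, so the pilot effect need not be the RCT's effect. The same data also inform the choice of outcome. If that choice looked at between-group differences, it would favour scales that came out well by chance.

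What is at stake is the power of the later RCT.

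**Working it through.** **Inputs from the article:** 60 per group; five scales given to all patients; four diagnoses (bipolar disorder, schizophrenia, schizoaffective disorder, severe recurrent major depression).

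**Assumed, because the article gives no value:** RCT alpha 0.05 two-sided; target power 80%; true standardised effect d = 0.2, 0.3 or 0.5; dropout 0% or 20%; correlation between scales 0.3 to 0.7; even split across diagnoses. The article gives no calculation behind 60 + 60, so there is no figure to reproduce.

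**1. Precision.** SE(d) ≈ √(2/n) and half-width = 1.96 × SE.

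| Per arm | SE | 95% half-width |
|---|---|---|
| 60 (no dropout) | 0.183 | ±0.36 |
| 48 (20% dropout) | 0.204 | ±0.40 |
| 30 (a scale serving two of four diagnoses) | 0.258 | ±0.51 |
| 15 (a scale serving one of four diagnoses) | 0.365 | ±0.72 |

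**2. Sample size implied for the RCT.** n per arm = 2(1.960 + 0.842)²/d² = 15.70/d². At d = 0.30 this is 175. With true d = 0.30, 95% of pilot estimates lie between 0.30 − 0.36 = −0.06 and 0.30 + 0.36 = 0.66. The upper end gives 37 per arm; the lower end gives no usable size.

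**3. Chance of missing target power.** With n taken from the pilot estimate e, true power = Φ(2.802 × d/e − 1.960).

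- Power is below 80% whenever e > d. For an unbiased, symmetric estimate that probability is 0.50. Counting large negative estimates by their magnitude, the chance of reaching target is 0.486, 0.499 and 0.500 at d = 0.2, 0.3 and 0.5. Among positive estimates only, it is 0.42, 0.47 and 0.50. The noncentral t distribution also gives about 0.50.
- Power is below 50% whenever e > d × 2.802/1.960 = 1.43d. At d = 0.30: 1 − Φ(0.429 × 0.30/0.183) = 1 − Φ(0.706) = 0.24. The same formula gives 1 − Φ(0.470) = 0.32 at d = 0.2 and 1 − Φ(1.176) = 0.12 at d = 0.5.

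**4. Bias.** If the estimate is off by b, the chance of reaching target is about Φ(−b/0.183). This is 71% at b = −0.1 and 29% at b = +0.1. The article gives no basis for knowing the sign of b.

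**5. Conditional case: outcome chosen by largest observed difference.** Take five scales with equal true effects of 0.30 and correlation 0.5. The expected maximum of five independent standard normals is 1.163, so the average inflation is 1.163 × 0.183 × √0.5 = 0.15. The selected estimate averages 0.45, which gives 15.70/0.45² = 78 per arm instead of 175. Real power is then Φ(0.30/√(2/78) − 1.960) = Φ(−0.087) = 47%. Over correlations 0.3 to 0.7 the range is 69 to 91 per arm and 42% to 53% power. The chance of reaching target is 0.17 at correlation 0.5. It rises to 0.30 if the true effects instead run from 0.4 down to 0.

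**6. The alternative.** Fix the outcome and target difference in advance and take only the SD from the pilot (118 degrees of freedom). If the true effect equals the target difference, median power is about 80%, and power is at least 73% in 90% of pilots. Using the upper 80% limit of the SD multiplies n by 118/χ²(0.20; 118) = 1.12.

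**The case against.** The strongest reply is that the article speaks only of informing a choice and helping to estimate a size. Other inputs are not excluded, safeguards may stand in the preregistration, and the RCT's sizing belongs to the RCT's own protocol. That limits the severity, but it does not remove the point: using effect estimates for the power calculation is a declared purpose, not a missing detail.

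Four stronger readings are tempting, and the documents do not support them.

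- **That the outcome will be picked by its largest effect.** The article does not say so. The most suitable outcome could equally be judged on completeness or responsiveness, which would leave the chance near 50%. The 78 per arm and 47% power are therefore conditional, and they also assume equal true effects.
- **That an even chance is an upper bound.** It holds only for an unbiased estimate taken at face value. A downward bias, for example because the refined prototype works better, would raise the chance. Nor is the 50% peculiar to 60 per group: a larger pilot would only make the misses smaller.
- **That a poor estimate could wrongly end development.** The Abstract's conclusions and the Discussion on pharmacotherapy tie progress to feasibility. No effect-based stopping criterion is stated.
- **That the diagnosis-specific scales are all as imprecise as ±0.72.** That is the worst case. A psychosis scale could serve both schizophrenia and schizoaffective disorder, giving about ±0.51 on the same even split. The article also says that self-rated and clinician-rated scales were chosen to explore correlations with the ePRO items, so it is an inference that the diagnosis-specific ones are candidates for the RCT's primary outcome.

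**Conclusion.** The point holds, at moderate severity. Effect estimates from 60 versus 60 patients carry a 95% half-width of about ±0.36 (about ±0.40 at an assumed 20% loss, wider for diagnosis-specific scales). An RCT sized on an unbiased estimate at face value would miss 80% power about half the time at assumed d of 0.2, 0.3 or 0.5. At d = 0.30 its power would be below 50% in about 24% of cases. Possible confounding and the change of prototype add bias of unknown direction. Further inflation from choosing the outcome arises only if that choice uses the between-group difference, which the article does not state. The pilot's adherence, retention and usability aims are untouched; the risk falls on the later RCT.

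**What to change.** In the pilot-planning section and the preregistration, replace the clause on effect estimates with wording such as:

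> The RCT will be sized on a minimal important difference fixed before any pilot outcome data are seen. The pilot will supply standard deviations (upper confidence limit), baseline–follow-up correlations, retention and completeness. The RCT primary outcome will be chosen on completeness, floor and ceiling effects and relevance across diagnoses, without reference to the between-group difference. Between-group differences will be reported with 95% confidence intervals, as descriptive only.

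The change is one of wording, but it has to be made before pilot outcome data are seen, because a choice of outcome blind to the group difference cannot be recovered afterwards. The cost is that the RCT may come out larger than a favourable pilot estimate would suggest. Using the upper 80% limit of the SD adds about 12% more patients.
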